# Study Protocol for the Evaluation of Multidisciplinary Medication Reconciliation Service in Adult Patients Undergoing Thoracic and Cardiovascular Surgery (The MERITS Study): A Single-Center Controlled before-and-after Study

**DOI:** 10.3390/healthcare11121778

**Published:** 2023-06-16

**Keywords:** medication reconciliation, multidisciplinary, transition of care, best possible medication history

## Abstract

Medication reconciliation (MR), which is widely implemented worldwide, aims to improve patient safety to reduce the medication errors during care transition. Despite its widespread use, MR has not yet been implemented in the Republic of Korea, and its effectiveness has not been studied. We aimed to evaluate the impact of a multidisciplinary MR service in older patients undergoing thoracic and cardiovascular surgery. This is a single-center, prospective, controlled, before-and-after study of adult patients taking at least one chronic oral medication. Depending on the period of each patient’s participation, they will be allocated to an intervention group or control group. Patients in the intervention group will receive multidisciplinary MR, and those in the control group will receive usual care. The primary outcome is to assess the impact of the MR service on medication discrepancies between the best possible medication history and medication orders at care transition. Secondary outcomes include the incidence rate of medication discrepancies at each transition, the discrepancy rate between the sources of information, the impact of MR on medication appropriateness index score, drug-related problems, 30-day mortality, the emergency department visit rate, readmission rate after discharge, the rate and acceptability of pharmacists’ intervention during hospitalization, and patients’ satisfaction.

## 1. Introduction

Transition of care can be a vulnerable moment for patients, as it often involves changing medication regimen and medication discrepancies, and gaps in communications can lead to medication errors and potential harm. According to a systematic review, 27%–54% of patients had at least one unintentional medication discrepancy that could result in drug-related problems (DRPs), which actually or potentially harmed patients [1]. Ema et al. found that 63.7% of patients experienced at least one DRP after the discharge and also showed that DRPs were more likely to occur when patients had multiple medication changes [2]. Moreover, among the medication errors related to reconciliation issues, 22% occurred during patient admission, 12% occurred during discharge and one-third occurred during the transition of care [3].

To improve medication safety at transition points of care, medication reconciliation (MR) was first adopted as a National Patient Safety Goal by the Joint Commission in 2005 and suggested as an imperative process by international health organizations [4]. In addition, the World Health Organization (WHO) has prioritized this area as a critical commitment to protect patients from medication-related harm during transitions of care [5].

MR is defined as a formal process of identifying an accurate list of a person’s best possible medication history (BPMH) and comparing it with the current list in use, recognizing any discrepancies and documenting any changes. The BPMH is obtained through a systematic process that involves interviewing the patient, their family members or caregivers. The information gathered during the interview is then verified by cross-referencing it with at least one other reliable source of information [4]. Previous systematic reviews have shown that MR significantly reduces the rate of adverse drug events that lead to outpatient visits by 67%, emergency department visits by 28%, and hospital readmissions by 19% compared to usual care [6]. Furthermore, a systematic review published in 2019 reported that the risk of medication errors was 75% lower when MR was conducted (risk ratio 0.25; 95% CI 0.15–0.43) [7].

While MR has been implemented in routine clinical practice in many countries worldwide [5], the systematic introduction and implementation of MR services have not yet been established in the Republic of Korea. The lack of understanding or awareness regarding the incidence of medication discrepancies or DRPs during care transition periods in the Republic of Korea may hinder the active adoption of this system.

We will attempt to introduce and evaluate the “Multidisciplinary Medication Reconciliation service in adult patients undergoing Thoracic and cardiovascular Surgery” (MERITS trial). The primary goal is to assess the impact of the multidisciplinary MR service on medication discrepancies during transitions of care. By evaluating these outcomes, the MERITS trial hopes to demonstrate the benefits of a multidisciplinary MR service in improving medication management and patient outcomes in transitional care.

## 2. Materials and Methods

### 2.1. Design

This study was reviewed and approved by the Institutional Review Board of Seoul National University Hospital (IRB No 2109-135-1257). This is a single-center, prospective, controlled, before-and-after study comparing two patient care strategies: (1) the control group, receiving standard care; (2) the intervention group, receiving multidisciplinary MR service. Depending on the time period of each patient’s participation, they will be assigned to either the control group or the intervention group. The study will initially enroll patients into the control group. Once the enrollment for the control group is completed, the study will proceed to enroll patients into the intervention group. Study enrolment started in December 2021, and the study is expected to be completed within 3 years. There are two phases in this study. Phase 1 (control group) will last about four months, and phase 2 (intervention group) will last eight months.

### 2.2. Setting

This study will be carried out in the Seoul National University Hospital (SNUH). It is located in the metropolitan area, and is a 1793-bedded tertiary hospital. The study will be conducted in five wards where patients undergoing thoracic and cardiovascular surgery are hospitalized.

### 2.3. Inclusion and Exclusion Criteria

Patients undergoing thoracic and cardiovascular surgery during the study period will be eligible for inclusion if they are 65 or older, are vulnerable to DRP [8,9] and are taking more than one chronic oral medication for an underlying comorbid disease before surgery. Patients who (1) have less than 48 h of hospital stay, (2) are unable to understand or complete questionnaires, (3) died during hospitalization, (4) are lost to follow-up, or (5) are considered inappropriate to enroll, for example, for being unable to understand Korean or having a diagnosis of dementia, by the medical staff will be excluded. Patients who meet all inclusion criteria and none of the exclusion criteria will be asked to participate in the study and provided with all the relevant information both verbally and in writing. The patients will not be informed about which group they have been assigned to in order to maintain blinding. If they decide to participate, they will be asked to sign an informed consent form and assigned to a group (Figure 1).

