#### 2.5.2. Secondary Outcome

The secondary endpoints are to (1) estimate the incidence rate of medication discrepancies at each transition and the discrepancy rate among the sources of information, (2) explore the impact of MR services on the medication appropriateness index (MAI) score [12], the rate of DRPs within 14 days and 30 days after discharge, 30 day mortality, ED visit rate, and readmission rate after discharge, (3) investigate the rate and acceptability of pharmacist interventions during hospitalization, and (4) explore patient satisfaction among the intervention group.

The DRP characteristics will be described using the Pharmaceutical Care Network Europe (PCNE) DRP classification [13]. The incidence rate of medication discrepancies will be calculated by dividing the number of patients with at least one discrepancy by the total number of patients in each group.

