### 2.6. Sample Size

The sample size calculation is based on the previous literature that referred to the incidence of medication discrepancies. The percentage of patients with at least one medication discrepancy varied based on ranged from 14.1% to 81.9% based on population and illness [14,15,16,17]. In a prospective French study, after proactive MR, the proportion of patients with at least one medication discrepancy decreased significantly from 45.8% to 2.07% (*p* < 0.001) [18]. Another study assessed MR in patients scheduled to undergo surgery, and the medication discrepancy rate in the intervention group decreased from 40.2% to 12.9% compared to that in the non-intervention group [19]. Using the reference rate of medication discrepancies reported in a previous study, it was estimated that 40% of the patients could experience at least one medication discrepancy, and the intervention may reduce these discrepancies by 40%. Assuming an alpha error of 5%, statistical power of 80%, and a 10% patient loss, the calculated sample size was 216 for the intervention group and 108 for the control group.

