### 2.8. Statistical Analysis

An intention-to-treat analysis will be conducted. The baseline characteristics will be summarized with descriptive statistics. Primary and secondary endpoints, except the rate and acceptability of pharmacist interventions during hospitalization, will be compared between the control and intervention groups. Categorical variables will be analyzed using the chi-square test or Fischer’s exact test, and continuous variables will be analyzed using the Student’s *t*-test or Mann–Whitney test. Data analysis will be performed after the data for the entire sample have been collected, using SAS version 9.4 (2017 SAS Institute, Cary, NC, USA) with a significance level of 0.05 and the limits of a confidence interval of 95%.

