## Figures and Tables

**Figure 1 healthcare-11-01778-f001:**
[figure not shown]
Flow of the intervention group (Phase 2) and control group (Phase 1).

**Table 1 healthcare-11-01778-t001:** Study procedure of MERITS study.

Time Point	Study Period				
	Enrolment and Allocation	Post-Allocation			
	Admission	Hospitalization	Discharge	First Outpatient Visit (about 2 Weeks after the Discharge)	30 Days after the Discharge

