**Assessments**					
Baseline characteristic	X	X			
Clinical Frailty Score		X			
Medication discrepancies	X	X	X		
Number of pharmacist interventions		X			
Medication appropriate index score			X		
Patient’s satisfaction				X	
Drug-related problems				X	X
Readmission				X	X
Emergency department visit				X	X
All-cause death				X	X

“X” and arrows show the data collection time points.

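### Excluding patients who die in hospital or are lost to follow-up removes enrolled patients by later events, contradicts the stated intention-to-treat analysis, and limits 30-day mortality to patients discharged alive and followed

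*Protocol article*

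**What the plan says.** All references are to the protocol article.

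- **Section 2.3** lists among the exclusion criteria patients who "3) died during hospitalization, (4) are lost to follow-up". It then states: "Patients who meet all inclusion criteria and none of the exclusion criteria will be asked to participate in the study". As written, every exclusion is settled before the invitation to join.
- **Table 1** marks the eligibility screen, informed consent and allocation in the admission column, under "Enrolment and Allocation".
- **Section 2.8** states "An intention-to-treat analysis will be conducted" and does not redefine the term.
- **Section 2.5.2** lists among the secondary outcomes "30 day mortality, ED visit rate, and readmission rate after discharge". In Table 1, "All-cause death" is marked only at the first outpatient visit and at 30 days after discharge.
- **Table 1** marks "Medication discrepancies", the basis of the primary outcome, at admission, hospitalization and discharge.
- **Section 2.4.1** has nurses obtain control patients' pre-admission medications. The pharmacist's assessment of those medications, with identification of discrepancies, is described at the first outpatient visit, around 14 days after discharge. **Section 2.4.2** has pharmacists obtain the best possible medication history before surgery in the intervention group.
- **Section 2.6** allows for 10% patient loss.

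**The concern.** An exclusion criterion defines who may enter a study. Death during the stay and loss to follow-up happen after entry, so used as exclusions they define who may leave the analysis, according to what happened to them. The set that remains is patients who survived to discharge and were followed, which is not an intention-to-treat set.

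The two groups are recruited in successive periods without randomisation (section 2.1). If deaths or losses differ between the periods in number or in kind, their removal shifts the comparison, and the analysed data cannot show it. The primary outcome is exposed because its transitions all precede the post-discharge follow-up: a patient lost after discharge has passed every transition, and one who dies in hospital has at least passed admission.

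Mortality is affected more directly. In-hospital deaths cannot appear in the results, and a death after discharge can also disappear if the patient cannot be reached and is classed as lost.

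**Working it through.** **1. The plan's own sample size.** Inputs from section 2.6: "it was estimated that 40% of the patients could experience at least one medication discrepancy", a 40% relative reduction, alpha 5% (two-sided assumed), power 80%, and 10% loss. The allocation of two intervention patients to one control follows from 216 and 108.

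- Intervention rate: 0.40 × (1 − 0.40) = 0.24. Difference: 0.16.
- Pooled rate: (0.40 + 2 × 0.24)/3 = 0.2933.
- Control n = [1.960 × √(1.5 × 0.2933 × 0.7067) + 0.842 × √(0.40 × 0.60 + 0.24 × 0.76/2)]² / 0.16² = 97.2, so 98 control and 196 intervention.
- With loss: 98 × 1.1 = 107.8 and 196 × 1.1 = 215.6, so 108 and 216.

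The stated figures reproduce. Power is 83.9% with all 108/216 analysed and 79.9% with 97/194. The sample size is therefore not the problem; the question is who is analysed.

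**2. Timing.**

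| Event | When it is known |
|---|---|
| Screening, consent, allocation | Admission (Table 1) |
| Death during hospitalization | During the stay |
| Loss to follow-up | After enrolment; for the scheduled follow-up, at about 14 or 30 days after discharge |

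Both exclusion events come after allocation. Section 2.3 (exclude) and section 2.8 (intention-to-treat) cannot both be followed.

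**3. How far removal could move the primary comparison.** Assume the 10% allowance is the share removed: 11 of 108 controls and 22 of 216 intervention patients, leaving 97 and 194. Take the planned rates among those kept, in whole patients: 39/97 = 40.2% and 47/194 = 24.2%, a difference of 16.0 points (chi-square without correction, p = 0.005).

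The removed share is d = 11/108 = 22/216 = 10.2%. Then

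difference over all enrolled = (1 − d) × difference among kept + d × (rate in excluded controls − rate in excluded intervention patients).

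| Excluded patients | Control | Intervention | Difference |
|---|---|---|---|
| Controls none, intervention all with a discrepancy | 39/108 = 36.1% | 69/216 = 31.9% | 4.2 points (p = 0.45) |
| Same rate in both groups | – | – | 0.898 × 16.0 = 14.4 points |
| Controls all, intervention none | 50/108 = 46.3% | 47/216 = 21.8% | 24.5 points |

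**4. Mortality.** The documents give no death rates, so these are assumptions: in-hospital death q from 1% to 5%, and death within 30 days after discharge r from 0.5% to 2% of those discharged, among 108 + 216 = 324 patients.

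- Share of all deaths removed = q / [q + (1 − q) r]. Lowest: 0.01/(0.01 + 0.99 × 0.02) = 34%. Highest: 0.05/(0.05 + 0.95 × 0.005) = 91%.
- Expected deaths still counted = 324 × (1 − q) × r. Lowest: 324 × 0.95 × 0.005 = 1.5. Highest: 324 × 0.99 × 0.02 = 6.4.

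**The case against.** Several points on the other side stand.

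- **Mortality is not emptied.** A reader might infer that the exclusions leave nothing to count. Table 1 collects deaths after discharge, and section 2.5.2 lists mortality beside outcomes after discharge, so a purely post-discharge outcome is a natural reading. On that reading the absence of in-hospital deaths is the outcome's scope. What remains is that the text does not clearly fix the origin. If the 30 days run from surgery or admission, early deaths are deleted from the outcome itself.
- **Removed patients do not all have primary-outcome data.** A reader might infer this from Table 1. Section 2.4.1 makes it insecure for controls: one who dies or misses the first outpatient visit may have only the nurse's list and no best possible medication history. The two places pull in different directions. This limits what can be recovered, but it also means that removal may act differently in the two phases.
- **The stay under 48 h** can be read as a planned stay, judged at admission. It needs clearer wording and does not show the same contradiction.
- **The bounds are extremes.** Nothing in the documents makes either one likely, and 10% is a planning allowance, not an estimate of deaths or exclusions. Quoting only the adverse bound would be one-sided.
- **Some restriction is unavoidable.** Patients who die in hospital have no post-discharge drug-related problems, emergency visits or readmissions.
- **No randomisation is being protected.** True, but the plan itself names intention-to-treat, and removal by later events adds a source of bias to a design that already lacks randomisation.

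**Conclusion.** The point holds as a contradiction within the document. The two criteria cannot operate at admission, so they remove enrolled patients by later events, and no other section reconciles this with the intention-to-treat statement. The choice decides who enters the primary analysis.

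On size, with 10% removed per group and the planned rates among those kept, the difference over all enrolled patients is bounded by about 4 and 25 points, against 16 among those kept. If the excluded patients had similar rates in both groups, the shift would be small (16.0 to 14.4 points). The risk lies in excluded patients who differ between phases. A reader might infer that the expected loss would overturn the result; the documents support only that it could, at one extreme.

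Mortality is restricted to patients discharged alive and followed, with its time origin not clearly fixed. The share of deaths left out, 34% to 91%, rests wholly on assumed rates and is a loss to the outcome only if in-hospital deaths were meant to count.

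**What to change.** 1. Delete in-hospital death and loss to follow-up as eligibility criteria. Word the 48 h criterion as an expected stay, judged at admission.
2. Analyse all consented patients in their phase of enrolment. Count discrepancies at each transition the patient reached. Analyse the discharge transition and the post-discharge outcomes in patients discharged alive.
3. Treat loss to follow-up as missing data only for outcomes that were not observed.
4. Reconcile section 2.4.1 with Table 1 on when the control group's comparison list is obtained. Where a control patient has no best possible medication history, treat the primary outcome as missing and run a sensitivity analysis. Do not substitute the nurse's list without saying so, since a weaker source in one phase could add its own bias.
5. State the time origin of 30-day mortality, and report in-hospital deaths by phase whichever origin is chosen.

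The cost is a change of wording, record retrieval for a few consented phase 1 patients, and some missing primary-outcome data that the present exclusions would hide. No extra enrolment is needed. Section 2.10 reports phase 2 as under way, and section 2.8 defers analysis until the whole sample is collected, so the change can still be made before the data are compared.

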### 2.4. Intervention

#### 2.4.1. Phase 1: Control group

Patients enrolled in the control group will receive the usual standard of care. Pre-admission medications will be obtained by nurses. During hospitalization, health professionals will measure frailty according to the Korean-translated version of the Clinical Frailty Scale (CFS) [10]. Patients will receive discharge medication counseling as a part of discharge summary from the medical team. However, pharmacists will not be involved in the discharge process. At the first outpatient visit after the discharge, which will take place around 14 days after the discharge, the patients in the control group will receive face-to-face medication counseling from pharmacists. The counseling will include an assessment of the patients’ preadmission medications, and an identification of any discrepancies and DRPs. The patients will also be asked whether they had any ED visits or unscheduled readmissions after discharge. Additionally, pharmacists will conduct a post-discharge phone call with patients 30 days after the discharge to enquire about any DRPs, ED visits, or unscheduled readmissions, and their causes. The patients will be interviewed and asked specific questions pertaining to various aspects related to their health and medication. These questions include inquiries about possible side effects, any new symptoms experienced, history of outpatient or inpatient visits following their discharge, and any changes made to their current medications.

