Upon discharge, pharmacists will review discharge medications and compare them with the BPMH. Any discrepancies will be addressed, and pharmacists will provide counselling regarding discharge medications and medication changes. They will also provide patient-friendly updated written medication lists that include information on newly added, changed, and discontinued medications. If a patient is discharged on the weekend, pharmacist-led counselling will be conducted via telephone on the next weekday.

At the first outpatient visit after discharge, pharmacists will meet the patients and enquire about their health and medication issues, including DRPs, ED visits, and unscheduled readmission. Additionally, patients will be asked to complete a survey that includes questions about their satisfaction with the MR service and whether their understanding of their medications has improved. Similar to the control group, the pharmacists will contact the patients by phone 30 days after discharge to obtain information about their health and medication issues, including DRPs, ED visits, and unscheduled readmissions.

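### From about day 14 to day 30 the comparator for the post-discharge secondary outcomes is usual care plus pharmacist counselling, not the usual care that the protocol names

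*Protocol article*

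**What the plan says.** The Abstract states that "those in the control group will receive usual care", section 2.1 describes the control strategy as standard care, and section 2.4.1 opens with "Patients enrolled in the control group will receive the usual standard of care". The same section keeps pharmacists away from discharge: "pharmacists will not be involved in the discharge process".

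Section 2.4.1 then describes the first outpatient visit, "which will take place around 14 days after the discharge". There, "the patients in the control group will receive face-to-face medication counseling from pharmacists". The content includes an assessment of pre-admission drugs and "identification of any discrepancies and DRPs". For the intervention arm at the same visit, section 2.4.2 says that "pharmacists will meet the patients and enquire about their health and medication issues, including DRPs, ED visits, and unscheduled readmission", and adds a satisfaction survey. It names no counselling at that visit.

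Section 2.5.2 lists as secondary outcomes "the rate of DRPs within 14 days and 30 days after discharge", together with 30-day mortality, ED visits and readmission. Section 2.8 compares these between the arms. Table 1 collects all four at the first outpatient visit and again at day 30. The limitations in section 3 do not mention the control-arm counselling.

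**The concern.** Medication review, detection of discrepancies and DRPs, and counselling by a pharmacist are components of the service under test (section 2.4.2). Once controls have received them, later control outcomes no longer describe usual care, although the document still labels them so.

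What is at stake is how the 30-day results are read. A small or null difference in ED visits, readmission or death could be reported as no benefit over usual care, when for the later part of follow-up the comparator had itself received a pharmacist review. The DRP contrast has a second difficulty: at the day-14 visit the two arms are, as described, examined with different intensity.

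**Working it through.** **1. Which outcomes fall before and after the visit (Table 1, sections 2.5.1 and 2.5.2)**

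| Outcome | When assessed | Reached by the day-14 counselling? |
|---|---|---|
| Medication discrepancies (primary) | Admission, hospitalisation, discharge | No |
| Medication appropriateness index | Discharge | No |
| DRPs within 14 days | First outpatient visit | Care up to then, no; detection at the visit may differ by arm |
| DRPs within 30 days | First outpatient visit and day 30 | Yes, after about day 14 |
| ED visits, readmission, death | First outpatient visit and day 30 | Yes, after about day 14 |

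**2. Share of follow-up time.** (30 − 14)/30 = 16/30 = 53%. This is calendar time. The document does not say how events are spread over the 30 days.

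**3. The plan's own figure.** The protocol gives no 30-day rate or power. Its only calculation (section 2.6) concerns the primary outcome: 40% against 24% (a 40% relative reduction), 80% power, alpha 5% (taken as two-sided), 2:1 allocation. With pooled variance and p̄ = (0.40 + 2 × 0.24)/3 = 0.293,

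n(control) = [1.960 × √(1.5 × 0.293 × 0.707) + 0.842 × √(0.40 × 0.60 + 0.24 × 0.76/2)]² / 0.16² = 97.2, so 98 control and 196 intervention.

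Multiplying by 1.10 gives 107.8 and 215.6, that is 108 and 216 as stated. This point does not touch that figure. After 10% loss about 97 and 194 remain, and these numbers are used next.

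**4. Illustration of dilution for ED visits, readmission or death. Every rate here is an assumption.** Let c be the 30-day control rate under untouched usual care, RR = 0.60 the true risk ratio, s the share of control events after day 14, and f the fraction of the service's later effect that the counselling gives to controls. Then

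observed control rate = c × [1 − s × f × (1 − RR)] = c × (1 − 0.4 × s × f), and observed RR = 0.60 / (1 − 0.4 × s × f).

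| s | f | Observed RR | Power, c = 0.40 | Power, c = 0.20 |
|---|---|---|---|---|
| any | 0 | 0.60 | 80% | 45% |
| 0.25 | 0.25 | 0.62 | 75% | 41% |
| 0.25 | 0.50 | 0.63 | 70% | 37% |
| 0.25 | 1 | 0.67 | 57% | 29% |
| 0.50 | 0.25 | 0.63 | 70% | 37% |
| 0.50 | 0.50 | 0.67 | 57% | 29% |
| 0.50 | 1 | 0.75 | 31% | 17% |

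The movement is always towards no difference. Its size ranges from nothing to substantial, and the document offers no basis for choosing a row.

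**5. DRPs.** Two mechanisms oppose each other. Counselling may prevent later DRPs in controls, which shrinks the difference. A fuller review at the visit may find more DRPs in controls than enquiry finds in the intervention arm, which widens the difference in favour of the service. The net direction cannot be derived from the text.

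**The case against.** The strongest reply has four parts.

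- **Reach.** Only the later part of some secondary outcomes is touched, and section 2.5.2 says these are to be explored. A reader might infer that the 30-day comparisons as a whole are not against usual care. The document does not support that, because days 0 to 14 of each outcome are accrued before the counselling. This part stands.
- **Treatment or identification.** Section 2.4.1 says that control DRPs and discrepancies are identified, not that they are resolved. Working with doctors to resolve them is described only for the intervention arm, during hospitalisation (section 2.4.2). A reader might infer that controls are certainly part-treated, or that the effect is understated by some set fraction such as a quarter. Neither follows, since any such fraction needs assumed event timing and an assumed counselling effect. This stands too.
- **Routine practice and data collection.** The article does not say whether outpatient pharmacist counselling already belongs to usual care at this hospital, and a pharmacist contact at that visit is how outcomes are collected in both arms. The second half is right: the asymmetry lies in the counselling and fuller review, not in the contact or in asking about DRPs. On the first half, the Introduction says that reconciliation services are not established in the country, which makes a study-added procedure the likelier reading. Only the sponsor can settle it.
- **Splitting at the visit.** Taking outcomes up to the visit and before counselling would not work well. DRP identification is part of the counselling, the control phase is over (section 2.10 reports phase 2 under way), and an event can change or prevent the visit, so a patient-specific cut can depend on the outcome. This stands, and is why the fix uses a fixed day.

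None of this removes the mismatch between the stated comparator and the care described.

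**Conclusion.** The point holds in limited form. Unless the sponsor confirms that the day-14 counselling is routine at the hospital, the comparator from about day 14 to day 30 for DRPs, ED visits, readmission and death differs from the one named in the Abstract and sections 2.1 and 2.4.1, and the limitations do not say so. The sample size is untouched.

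If the counselling does anything, the ED-visit, readmission and death contrasts are diluted; the amount is unknown, and the table above is illustration only. For DRPs neither dilution nor inflation can be claimed. The point should be corrected before the 30-day results are interpreted, but it does not threaten the main conclusion of the study.

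**What to change.** 1. Reconcile the Abstract and sections 2.1, 2.4.1 and 2.5.2. Describe the 30-day contrasts as MR service versus usual care plus pharmacist counselling at about day 14, and list this in the limitations. If the counselling is already routine at the hospital, say so instead.
2. Add a comparison of dated ED visits, readmissions and deaths within a fixed 14 days after discharge, alongside the 14-day DRP endpoint already planned. Rest any post-discharge statement against usual care on that window.
3. Report the 30-day results with the comparator named.
4. Interpret the DRP contrasts, at 14 days as well as 30, with a caveat that the control review at the visit is described as fuller than the intervention enquiry.

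**Cost.** Wording and one added analysis. Table 1 already collects these outcomes at both contacts, so no new data should be needed, provided that event dates were recorded or can be recovered. The 14-day window will hold fewer events and give less precise estimates. Visits that fall before day 14 leave slight contamination.
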